### Outcomes

2.4

The primary outcome will be the oral anticoagulation control, assessed by TTR. We will consider as secondary outcomes knowledge on warfarin therapy and self-reported adherence to oral anticoagulation.

The outcomes will be compared intra and intergroups, using pre-defined time points to measure outcomes before and after the intervention. TTR and self-reported adherence to warfarin therapy will be measured 6 months before starting the intervention (T0), immediately after intervention completion (T1) and at 3 (T2), 6 (T3), 9 (T4) and 12 (T5) months after intervention completion. To prevent patients from exhaustion and considering that knowledge takes time to change, this variable will be measured at T0, T1, and T5 (Fig. 3).

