### Sample size

2.5

Sample size was calculated using diggle.linear.power function of longpower package in the software R 3.4.4 version.^[21]^ The TTR will be prospectively assessed, from T0 to T5. We considered an absolute increase of 6% in TTR with standard deviation of 7.5,^[22]^ 80% power, level of significance of 0.05 and at least 15% of variation in the slope coefficient between intervention and control groups. The calculated sample was 71 individuals for each group, and we planned to include 20% additional patients to account for a follow-up loss, resulting in 85 individuals allocated in each group. Also, we used composite symmetry autocorrelation structure with a correlation of 0.80 between the times of data collection.

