### Statistical analysis

2.9

TTR will be calculated by the Rosendaal method using a linear interpolation of INR results. TTR will be calculated at least 2 INR measurements. For participants who had INR intervals higher than 56 days, we used INR values to calculate TTR for the valid intervals (<56 days) and afterward we used the independent TTR values to calculate the final TTR by the arithmetic mean.^[33]^

Categorical variables will be expressed as frequency and percentage. Symmetric continuous variables will be expressed as means and standard deviation while asymmetric data will be expressed as median, first quartile, and third quartile.

To evaluate significance of each variable in the outcomes, univariate models will be adjusted using generalized estimation equation (GEE) with appropriate distribution for each outcome (normal or gamma distribution for TTR and binomial distribution for knowledge and adherence). Wald tests will be performed for each variable coefficient using an initial significance level of 0.20. All variables identified as initially significant will be added to a multivariate model and significance level will be set at 0.05. One final GEE multivariate model will be presented for each outcome including exclusively significant coefficients. Post hoc analysis will include comparisons of outcome means (or probabilities) at different time points. Statistical analysis will be performed in R version 3.4.4.

Patient refusal, death or other situations that would make it difficult for the patient to continue in the study will be registered and they will be considered as an intention to treat for analysis. Important protocol modifications will be reported to REBEC.

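### Section 2.5 sizes the trial on one between-group TTR slope difference, but section 2.9 names no confirmatory test and adds time-point comparisons without saying what they decide

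*Protocol article*

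**What the plan says.** Section 2.4 (Outcomes) defines the primary outcome without a time point or contrast: "The primary outcome will be the oral anticoagulation control, assessed by TTR". TTR is measured at T0, then "immediately after intervention completion (T1) and at 3 (T2), 6 (T3), 9 (T4) and 12 (T5) months after intervention completion". On how it is compared: "The outcomes will be compared intra and intergroups, using pre-defined time points to measure outcomes before and after the intervention".

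Section 2.5 (Sample size) rests on one contrast. It uses a linear-slope power function with "at least 15% of variation in the slope coefficient between intervention and control groups", a compound-symmetry correlation of 0.80 between times, a two-sample design, 80% power and a 0.05 level.

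Section 2.9 (Statistical analysis) never names group or a group-by-time term. Each variable is screened in a univariate GEE at 0.20, and then: "All variables identified as initially significant will be added to a multivariate model and significance level will be set at 0.05". The final model for each outcome presents significant coefficients only. The section then adds: "Post hoc analysis will include comparisons of outcome means (or probabilities) at different time points". It does not say which comparisons these are, at what level they are tested, or whether they depend on an earlier test.

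**The concern.** The contrast that was sized is not the contrast that is tested. Section 2.5 commits the trial to one between-group slope difference, and section 2.9 does not carry it forward. Because only significant coefficients stay in the final model, the very term that answers the trial question can disappear when it is not significant. What then remains on TTR over time is a set of time-point comparisons with no stated rank, together with the within-group comparisons of section 2.4.

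Two things are at stake. First, the 0.05 level cannot be attached to a claim that the intervention works, because no test is named that would establish it. Second, within-group change is a poor basis for such a claim here. Patients enter because TTR is below 60%, and section 2.6 admits some on the July to December 2018 window alone. Some later rise is expected from regression to the mean without any intervention effect. Persistently low TTR at two screenings reduces this for the other patients but does not remove it.

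**Working it through.** **Step 1: the plan's own figure.** Inputs from section 2.5: "We considered an absolute increase of 6% in TTR with standard deviation of 7.5", correlation 0.80, power 80%, level 0.05 (two-sided assumed), slope difference 15%. The slope formula is

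n per group = 2(z₀.₉₇₅ + z₀.₈₀)² · SD² · (1 − ρ) / (Sxx · d²).

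Take d = 0.15 TTR points per month and times coded 0, 1, 3, 6, 9, 12 (both assumed), so Sxx = 271 − 31²/6 = 110.83. Then n = 2 × 7.849 × 56.25 × 0.20 / (110.83 × 0.0225) = 70.8, that is 71. And 71 × 1.2 = 85.2, that is 85. The stated numbers reproduce, and they reproduce as the size for a single slope contrast.

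This depends on the time coding, which section 2.5 does not give. With d = 0.15 throughout:

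| Times coded | n per group |
|---|---|
| 0, 1, 3, 6, 9, 12 | 71 |
| 0, 0, 3, 6, 9, 12 | 66 |
| 0, 5, 8, 11, 14, 17 | 42 |
| −6, 0, 3, 6, 9, 12 | 38 |
| 0, 1, 2, 3, 4, 5 | 449 |

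The 6-point increase does not enter this calculation. A plain comparison of two means with difference 6 and SD 7.5 would need 2 × 7.849 × 56.25 / 36 = 24.5, that is 25 per group.

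**Step 2: error if the time-point tests decide.** Assumptions: no effect at any time, no drift, no clinic difference, unadjusted two-sided 0.05 tests, any one significant result counts, and correlation 0.80 between times as in section 2.5. Between-group differences in means at T1 to T5 then correlate 0.80. Changes from T0 share the baseline, so their correlation is (1 − ρ) / [2(1 − ρ)] = 0.50. For five such tests with correlation r and c = 1.96,

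P(at least one) = 1 − ∫ φ(u) [Φ((c − √r·u)/√(1 − r)) − Φ((−c − √r·u)/√(1 − r))]⁵ du.

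This gives 12.7% at r = 0.80 and 18.3% at r = 0.50. The independence bound is 1 − 0.95⁵ = 22.6%. A simulation of 1,000,000 draws of both groups over T0 to T5 agrees with the integral and supplies the combined families:

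| Family of tests | Any significant result | Favouring the intervention only |
|---|---|---|
| One test | 5% | 2.5% |
| Five between-group, means | 12.7% | 6.4% |
| Five between-group, changes from T0 | 18.3% | 9.1% |
| Between-group plus five within intervention arm | 28.2% (means), 28.7% (changes) | 14.6% (means), 14.4% (changes) |
| Between-group plus within-group in both arms | 41.0% (means), 37.6% (changes) | not computed |

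**Step 3: error under alternatives.** One pre-specified between-group test gives 5% two-sided. Bonferroni at 0.01 on each of five contrasts gives 3.0% (r = 0.80) to 4.2% (r = 0.50). If change contrasts are read only after a significant five-degree-of-freedom group-by-time test, the family error under the global null is about 4%.

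**The case against.** The strongest reply is that the article condenses a fuller plan, and adjustment of follow-up contrasts is commonly left to a statistical analysis plan that is not available here. Section 2.9 attaches 0.05 to the multivariate model, not to the time-point comparisons. It labels those post hoc, which suggests a subordinate role, and describes one final model per outcome. No sentence says that any single significant time point counts as success. All of that stands. A reader might infer that the plan tests every time point at 0.05 and accepts any hit; the document does not say so, and the percentages are conditional on that reading.

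A reader might also quote 13% to 18% as the chance of a false improvement, set against 5%. That is not supported: those figures include results favouring control, and the matching figures are 6% to 9% against 2.5%. Nor is 29% a ceiling, since it leaves out within-group tests in the control arm.

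Two further points carry weight. The null model ignores any difference between the two clinics and any drift from selection on low TTR, so the percentages measure multiplicity only. And a linear slope is not obviously the right confirmatory quantity. Assumed between-group differences of 0, 6, 6, 3, 1, 0 points at months 0, 1, 3, 6, 9, 12 give a slope of (51 − 16 × 31/6) / 110.83 = −31.67/110.83 = −0.29 per month. An early benefit that wanes would appear as harm.

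What the reply does not remove is the mismatch inside the stated text. Section 2.5 sizes one contrast, section 2.9 gives it no role, and the selection rule in 2.9 allows it to be dropped. That is not a detail left for later.

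**Conclusion.** The point holds in this form: section 2.9 names no confirmatory TTR test and does not carry forward the between-group slope contrast on which section 2.5 rests. This follows from the text and needs no assumption.

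Its numerical size is conditional. With unadjusted two-sided 0.05 tests and any one counted as success, a false significant result has probability 12.7% to 18.3% across the five between-group comparisons, about 29% with intervention-arm within-group tests and about 38% (changes from T0) with both arms. A false improvement has probability 6% to 9%, or about 14% with intervention-arm within-group tests, against 2.5%. If the time-point tests follow only a significant overall group-by-time test, there is no inflation under the global null, but section 2.9 states no such order. The documents do not support saying that the trial will have these error rates, only that the plan as worded does not exclude them.

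**What to change.** In section 2.9:

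- Name one between-group test of TTR over T0 to T5 as confirmatory, two-sided at 0.05. It can be the slope difference sized in section 2.5 or a joint group-by-time Wald test. The joint test does not presuppose a linear course.
- Keep that term in the model whatever its p-value, outside the 0.20 and 0.05 selection steps.
- Report the T1 to T5 between-group contrasts as secondary, either Holm-adjusted or as estimates with 95% confidence intervals and no significance claim.
- Report within-group changes descriptively only.

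In section 2.5, reconcile the calculation with the chosen test, and state the time coding and the units of the 15% slope difference.

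The cost is wording, plus a repeat of the sample-size calculation if the joint test is chosen, since it spends five degrees of freedom where the slope spends one. Claims about a single time point become slightly harder to make.

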## Discussion

3

This study will allow assessing the effect of a patient-centered intervention on patients taking warfarin in a population with low socioeconomic status. We will explore critical aspects of warfarin treatment, including TTR, knowledge, and adherence to warfarin therapy. The trial design will help investigating the effect of an educational intervention specifically tailored to empower patients with poor anticoagulation control. We expect to offer an innovative educational approach to help improving patient self-care and, consequently, achieving better therapeutic results.

AF has increased its prevalence worldwide. It is expected that a growing number of patients will have indication for oral anticoagulation, including those with low-income and inadequate health literacy.^[1,34]^ Patient education is a challenge in providing care to warfarin patients with limited socioeconomic status.^[8,9]^ Studies focusing on educational interventions can contribute to the creation of more effective strategies to be applied in patients with inadequate health literacy.

We believe that the employment of the principles of empowerment can help patients making better decisions for self-care. Although widely known, empowerment practices are little explored by studies involving health education in low- and middle-income countries. Paulo Freire's theory has proposed educational strategies that enrich patients’ previous experience, critical thinking, and a dialogical process.^[16,17]^ This must be built by educators and learners. These strategies may contribute to change patients’ behavior toward warfarin therapy and to improve adherence to the treatment and to the recommended diet, and also to increase TTR.

In our study, we will assess a real-world population treated in Brazilian ACs differing from other studies that involved highly selected populations with exclusion of people with inadequate health literacy and cognitive impairment. Previous studies conducted in ACs in Brazil showed that there is a stratum of patients with a persistent TTR <60% who could potentially benefit from health empowerment strategies to improve oral anticoagulation control.^[35,36]^ The strength of our study is that it can fill a gap in the scientific knowledge on the impact of educational interventions focused on low-income patients with AF and poor anticoagulation control. It stands out that low-income populations are not extensively studied. Several studies carried out in developed countries have pointed out difficulties to obtain results with health education actions in patients with inadequate health literacy population on warfarin.^[8,9]^ Another strength is that the settings of our study adopt similar standardized protocols for anticoagulation management bringing consistency to the comparisons of TTR.

To minimize selection bias, we will exclude patients with treatment duration <6 months to improve the homogeneity of the studied groups. We believe that patients using warfarin for <6 months (inception patients) would have different perceptions and behavior towards warfarin therapy than those using for >6 months (experienced patients).^[37]^ The allocation of patients in the intervention or control groups located in separated centers will reduce bias related to the interference of intervention over the control group. Researchers will not get involved in clinical practice during the conduction of the study. Their involvement could interfere in the standardized care provided to the intervention group. The measured outcomes—TTR, knowledge, and adherence to warfarin therapy—will be assessed at different time intervals, allowing short- and long-term evaluations of impact of the educational intervention. It is expected that the final results from this study will be available by July 2020.

As limitations, we should address that the studied patients will be randomized intragroup, but not intergroup. Moreover, we will not identify definitive outcomes, such as hemorrhagic and thromboembolic complications. This derives from the limitation of data collection regarding the history of previous of INR values and occurrence of adverse events. Patients who presented adverse events may have been admitted by other healthcare institutions hindering the access to patient clinical history.

Our study will allow testing the intervention in a real-world, in a country that has a significant proportion of patients with limited socioeconomic status, who do not have wide access to alternative anticoagulation therapies instead of warfarin. The perspectives of our findings include the potential to contribute for future strategies involving patients on warfarin assisted by the Brazilian Unified Health System (Sistema Único de Saúde—SUS). Besides, we believe that our findings can contribute to improve health education actions directed to low-income patients with AF treated with warfarin in other countries in the world.

## Declarations

4

Ethics approval and consent to participate: This study has been approved by the institutional Ethics’ Committee of the Universidade Federal de Minas Gerais (UFMG), under the code CAAE 65928316.3.0000.5149. All patients will be invited to provide a signed informed consent to participate in the study. This study has been registered at Registro Brasileiro de Ensaios Clínicos (REBEC) RBR- 9cy6py and UTN: U1111-1217-0151.
